### Sample size

All statistical tests were two-tailed and were considered to be statistically significant at *P* < 0.05. A sample size of 133 subjects was calculated accepting the following parameters: effect size medium = 0.30; alpha = 0.05; 1-ß = 0.80. Considering a drop-out rate of 15%, a total sample size of 153 smokers was determined. The smokers will be randomized into the three arms of our study protocol (51 smokers for each arm).

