### Study outcome measures

A reduction ≥50% in the number of cigarettes/day from BL, defined as self-reported reduction in the number of cigarettes/day (≥50%) compared to BL (together with an eCO levels reduction, to objectively document a reduction from baseline), will be calculated at each study visit (referred to as reducers). Abstinence from smoking, defined as complete self-reported abstinence from tobacco smoking - not even a puff (together with an eCO concentration ≤7 ppm), will be calculated at each study visit (referred to as quitters). Smokers who do not satisfy the criteria of reducers or quitters will be defined non responders. Smokers who leave the study protocol before its completion due to lack of efficacy or poor tolerability of the product under investigation, will carry out the early termination visit and will be defined as non responders.

AEs, symptoms thought to be related to tobacco smoking and e-cigarette use, and to withdrawal from nicotine, will be annotated at BL and at each subsequent study visit on the AE page of the study diary. Vital signs will be also recorded. The number and the percentage of subjects experiencing AEs, adverse reactions, serious AEs and AEs leading to study withdrawal will be summarized by treatment group. AEs will also be summarized by system organ class and preferred term using the *MedDRA* dictionary.

Quality of life, neurocognitive functioning and psychopathological status will be reassessed by QLS, BACS and PANSS, respectively. Participants’ perceptions and liking of the product will be assessed by asking them to rate their levels of satisfaction with the products compared to their own cigarettes using a VAS, scoring from 0 to 10 points (0 = completely unsatisfied, 10 = fully satisfied). Using the same scale, they will also rate how much they miss their own brand (0 = did not miss it at all, 10 = missed it too much) and whether they would recommend it to a friend/relative (0 = not recommended at all, 10 = absolutely recommended).

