### Statistical methods

Statistical analysis will be performed with SPSS 20.0 (Statistical Package for Social Sciences Program, IBM). Continuous variables will be described with mean, standard deviation, median, minimum, maximum and the 25th and 75th percentiles. Categorical variables will be described with percentages and absolute frequencies. The differences in continuous variables between the three groups will be evaluated with the Kruskal-Wallis test, followed by the Dunn multiple comparison test. The differences between the three groups for normally distributed data will be evaluated with one-way analysis of variance (ANOVA), followed by the Newman-Keuls multiple comparison test. The normality of the distribution will be evaluated with the Kolmogorov-Smirnov test. Any correlation between the variables under evaluation will be assessed by Spearman *r* correlation. To compare qualitative data we will use the Chi-square test with the Yates correction or the Fisher exact test.

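### The allowance for 15% drop-out is slightly too small: 153 randomized leaves about 130 evaluable smokers, not the 133 calculated

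*Protocol article*

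**What the plan says.** The Sample size section of the protocol article builds the total in two steps. First, "A sample size of 133 subjects was calculated accepting the following parameters", the parameters being "effect size medium = 0.30; alpha = 0.05; 1-ß = 0.80". Second, "Considering a drop-out rate of 15%, a total sample size of 153 smokers was determined". The 153 are then split equally: "The smokers will be randomized into the three arms of our study protocol (51 smokers for each arm"). The section does not print the formula that leads from 133 to 153, and it does not name the test or the effect-size index behind the 0.30.

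Two other sections bear on the point. Statistical methods says: "To compare qualitative data we will use the Chi-square test with the Yates correction or the Fisher exact test". Study outcome measures sorts smokers into reducers, quitters and non-responders, and says of those who leave early because the product did not work or was poorly tolerated that they "will carry out the early termination visit and will be defined as non responders". The abstract words this rule more broadly, without restricting it to those two reasons.

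**The concern.** A drop-out rate is a fraction of those randomized. The number to randomize is therefore the evaluable number divided by one minus the rate. Multiplying the evaluable number by one plus the rate always falls short, because the loss is then taken from the larger, inflated total. The stated 133, 15% and 153 cannot all hold together, whichever formula was used: 15% off 153 does not leave 133.

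What is at stake is whether the stated 80% power belongs to the trial at its own planned drop-out rate. The three figures will be read together as the justification for the trial's size, so they should agree.

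**Working it through.** **Inputs**

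- Evaluable number 133, effect size 0.30, alpha 0.05, power 0.80, drop-out 15%, total 153, 51 per arm: all from Sample size.
- Two-tailed testing at the 5% level: same section, "All statistical tests were two-tailed and were considered to be statistically significant at *P* < 0.05".
- Three outcome categories (reducer, quitter, non-responder): Study outcome measures. With three arms this gives (3 − 1) × (3 − 1) = 4 degrees of freedom. That link is an inference; the article does not make it.

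**Step 1. Reproduce the 133.** For a chi-square test, power is the probability that a non-central chi-square variable with non-centrality N × w² exceeds the 95th percentile of the central distribution. With w = 0.30, the smallest N giving 80% power is:

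| Basis | N |
|---|---|
| Chi-square, 1 df | 88 |
| Chi-square, 2 df | 108 |
| Chi-square, 3 df | 122 |
| Chi-square, 4 df | **133** |
| One-way ANOVA, 3 groups, f = 0.30 | 111 |
| One-way ANOVA, 3 groups, f = 0.25 | 158 |
| Two means, d = 0.30 | 175 per arm |

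Only the 4-df chi-square gives 133, with non-centrality 133 × 0.09 = 11.97 and power 80.1%.

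**Step 2. Reproduce the 153.**

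- Multiplying: 133 × 1.15 = 152.95, which rounds to 153. This matches the article.
- Dividing: 133 / 0.85 = 156.47, which rounds up to 157. Three equal arms need 3 × 53 = 159.

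**Step 3. What 153 delivers at 15% loss.** 153 × 0.85 = 130.05, so about 130 evaluable. The shortfall against 133 is 3 smokers, or 3 / 133 = 2.3%.

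**Step 4. What loss 153 can absorb.** (153 − 133) / 153 = 20 / 153 = 13.1%.

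**Step 5. Power, on the inferred basis (w = 0.30, 4 df).**

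| N analysed | Non-centrality | Power |
|---|---|---|
| 130 | 130 × 0.09 = 11.70 | 79.1% |
| 133 | 133 × 0.09 = 11.97 | 80.1% |
| 153 | 153 × 0.09 = 13.77 | 86.0% |

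With 130 evaluable, the w detectable with 80% power is 0.303 instead of 0.300.

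**The case against.** The best defence is that this hardly matters. The gap is three smokers and about one point of power, and the detectable effect barely moves. The 15% is itself a planning guess, and a true loss of 13% would make the paragraph correct. This stands, and it sets the size of the point. It does not make the printed figures agree.

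A second defence is that some drop-outs are not lost at all. Study outcome measures keeps those who leave for want of effect or tolerability in the responder outcome as non-responders. If the 0.30 describes the outcome after that classification and everyone is analysed, all 153 count and power is 86.0% on the inferred basis. This also stands. For that reason the documents do not support a stronger claim that a reader might infer, namely that the stated power fails however drop-outs are handled.

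A reader might argue the other way: counting drop-outs as failures dilutes the effect, so power must fall clearly below 80%. That can happen if the 0.30 describes completers, but no figure follows from this article. It would need response rates by arm, the pattern of differences between arms and the share of leavers classed as non-responders, and none of these is given. The answer also depends on the table chosen. Assume one differing arm, 20–40% overall response and 15% of each arm turned into non-responders. A responder yes/no table then gives w of about 0.26–0.27, and at N = 153 its own 2-df test has 84–86% power. Using the same w on 4 df gives 75–77%, but that pairs an effect size from one table with the test for another.

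A reader might also take the 80% as the power to show that the e-cigarette beats the inhalator. The section makes no claim about any pair of arms, and a condensed article may leave such detail to the full protocol or analysis plan.

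**Conclusion.** The point holds as a minor arithmetic correction. The stated 133, 15% and 153 are inconsistent: 153 matches multiplication by 1.15, and at 15% loss it leaves about 130 evaluable smokers. This rests only on the article's own figures. That the multiplication was actually used is inferred from the match.

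The effect on power, about 79% instead of 80%, rests on two further conditions: that 133 came from a chi-square test with w = 0.30 and 4 df, and that drop-outs leave the analysis. The first is inferred because it reproduces 133. The second is unsettled for the responder outcome, because the article does not say whether the 0.30 applies before or after some drop-outs are classed as non-responders. The finding does not show that the trial is materially underpowered.

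**What to change.** Keep 153 and restate the Sample size paragraph along these lines: *153 randomized gives about 130 evaluable and about 79% power at 15% loss, or 133 evaluable and 80% power with up to 13% loss.* Before this is printed, the sponsor should confirm the test, effect-size index and degrees of freedom behind the 133, since the 79% depends on them.

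Add one sentence saying whether the 0.30 applies before or after early leavers are classed as non-responders, so that the drop-out allowance and the outcome definition rest on the same assumption. No diluted or pairwise power figure should be added on the strength of this article alone.

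The cost is a reworded paragraph and a stated power about one point less favourable. No extra smokers are needed, and the 51 per arm and 51 per centre stay as they are.

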### Statistical methods

Statistical analysis will be performed with SPSS 20.0 (Statistical Package for Social Sciences Program, IBM). Continuous variables will be described with mean, standard deviation, median, minimum, maximum and the 25th and 75th percentiles. Categorical variables will be described with percentages and absolute frequencies. The differences in continuous variables between the three groups will be evaluated with the Kruskal-Wallis test, followed by the Dunn multiple comparison test. The differences between the three groups for normally distributed data will be evaluated with one-way analysis of variance (ANOVA), followed by the Newman-Keuls multiple comparison test. The normality of the distribution will be evaluated with the Kolmogorov-Smirnov test. Any correlation between the variables under evaluation will be assessed by Spearman *r* correlation. To compare qualitative data we will use the Chi-square test with the Yates correction or the Fisher exact test.

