Study participants will attend a final follow-up visit at week 52 to report product use and the number of any tobacco cigarettes smoked (from which reduction and quit rates could be calculated), and to re-check eCO levels. Quality of life, neurocognitive functioning and psychopathological status will be assessed by QLS, BACS, and PANSS, respectively. Vital signs (HR and BP), body weight, and spirometry will be recorded again as well as participants’ perceptions of the specific product they are using [11].

Early termination visit (unscheduled visit) is as follows: CRF (number of cigarettes/day, eCO, HR, BP); craving/VAS; MNWS; PANSS; BACS; QLS; smokers’ product preference survey; spirometry (Table 1).

**Table 1 T1:** Study schedule

**Procedure**		**BL Visit**	**Wk4**	**Wk8**	**Wk12**	**Wk24**	**Wk52**	**Early termination visit**
		**Visit 1**	**Visit 2**	**Visit 3**	**Visit 4**	**Visit 5**	**Visit 6**	
Informed consent		**X**						
Inclusion/exclusion criteria (review)		**X**						
**CRF**	Sociodemografic factors	**X**						
	Smoking Hx	**X**						
	no. cig/day	**X**	**X**	**X**	**X**	**X**	**X**	**X**
	Physical examination	**X**					**X**	
	FTDC, GN-SBQ, QLS, BACS	**X**			**X**	**X**	**X**	**X**
	eCO	**X**	**X**	**X**	**X**	**X**	**X**	**X**
	HR, BP	**X**	**X**	**X**	**X**	**X**	**X**	**X**
	Weight	**X**				**X**	**X**	
	AEs	**X**	**X**	**X**	**X**	**X**	**X**	**X**
Randomization into either study group A (Ecig 24 mg), B (Ecig o mg), or C (paipo)		**X**						
Dispense 4-weeks supply of either nicotine or no-nicotine or paipo (depending on arm allocation)		**X**	**X**	**X**	**X (x3)**			
Dispense 4-weeks’ study diary for AEs		**X**	**X**	**X**	**X (x3)**			
Spirometry		**X**			**X**	**X**	**X**	**X**
Book for next appointment in 4 weeks (week-4; study visit 2)		**X**	**X**	**X**	**X (x3)**	**X(x6)**		
Craving/VAS		**X**	**X**	**X**	**X**	**X**	**X**	**X**
MNWS		**X**	**X**	**X**	**X**	**X**	**X**	**X**
PANSS			**X**	**X**	**X**	**X**	**X**	**X**

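### One-way, single-value tests are fixed for continuous outcomes measured repeatedly, with no stated place for the PANSS, QLS, BACS and spirometry values from the early termination visit

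*Protocol article*

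**What the plan says.** Statistical methods names two routes for continuous variables. The first is rank-based: "The differences in continuous variables between the three groups will be evaluated with the Kruskal-Wallis test, followed by the Dunn multiple comparison test". The second, for normally distributed data, is "evaluated with one-way analysis of variance (ANOVA), followed by the Newman-Keuls multiple comparison test". The section names no visit, baseline covariate or within-person term.

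Study outcome measures says: "Quality of life, neurocognitive functioning and psychopathological status will be reassessed by QLS, BACS and PANSS, respectively". It gives no analysis time point for these scales. The wording that ties a calculation to every visit is used for the smoking classes only, for example "will be calculated at each study visit (referred to as reducers".

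The same section has the only rule for people who leave. It states what happens to them: they "will carry out the early termination visit and will be defined as non responders". The reasons for leaving that it covers are limited to departures "due to lack of efficacy or poor tolerability of the product under investigation".

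Study schedule lists what the early termination visit collects beyond cigarettes per day, eCO and vital signs: "craving/VAS; MNWS; PANSS; BACS; QLS; smokers’ product preference survey; spirometry (Table 1".

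**The concern.** PANSS, QLS, BACS and spirometry show whether a product harms mental state, quality of life, cognition or lung function. They are measured several times in each person, but the named tests take one number per person and compare three groups. Baseline and all other visits then go unused.

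The people most likely to lack a late value include those whom the protocol itself describes as leaving over efficacy or tolerability, so absence may be related to outcome. Their early termination measurements are already planned. However, that visit is unscheduled, and the rule that makes a leaver a non responder cannot be applied to a PANSS or BACS score. A comparison at a fixed week would therefore omit those values unless a further rule brings them in. If leaving follows worsening more closely in one arm, that arm would look better than it is.

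**Working it through.** **1. Schedule against test.** From Study design, the visit summaries in Study schedule, and Table 1:

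| Instrument | Pre-treatment value | Follow-up weeks, visit text | Follow-up weeks, Table 1 | Early termination |
|---|---|---|---|---|
| PANSS | screening | 4, 8, 12, 24, 52 | 4, 8, 12, 24, 52 | yes |
| QLS, BACS | baseline visit | 24, 52 | 12, 24, 52 | yes |
| Spirometry | baseline visit | 24, 52 | 12, 24, 52 | yes |

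Kruskal-Wallis and one-way ANOVA each use one of these values, or one summary of them. The visit text and Table 1 disagree on week 12 for QLS, BACS and spirometry.

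**2. The plan's own figure.** Sample size gives effect size 0.30, alpha 0.05 and power 0.80. A chi-square test with w = 0.30 and noncentrality N × w² needs N = 133 at 4 degrees of freedom, which is an exact match. At 2 degrees of freedom it needs 108. One-way ANOVA with f = 0.30 needs 111. A table of three arms by three response classes has (3 − 1) × (3 − 1) = 4 degrees of freedom. The size therefore appears to rest on the smoking classes, although the article does not name the test. Then 133 × 1.15 = 152.95, which rounds to 153. No stated figure depends on the present point.

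**3. People affected.** 153 × 0.15 = 22.95, about 23 people; 153 × 0.85 = 130.05, about 130 remain.

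**4. Simple illustration (assumed values).** Suppose a share d of one arm leaves with outcomes h SD worse, and those who stay show no effect. The difference over all randomized people is d × h, while attendees show 0. With d = 0.15:
- h = 0.5: 0.15 × 0.5 = 0.075 SD
- h = 1.5: 0.15 × 1.5 = 0.225 SD

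**5. Simulation (assumed mechanism).** Only the 51 per arm and the drop-out of about 15% come from the article. Assumed: baseline plus five follow-up visits, outcome in SD units, equal correlation between visits of 0.5 to 0.8, and a leaving probability logistic in the current value with slope 1.3 per SD, or half of that. The half-slope rows and the no-difference, same-slope row were run for arm A against one comparator with 200,000 per arm. The others used 51 per arm and 1,500 runs. Arm A is the arm that may worsen.

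| True difference | Link between leaving and worsening | Week-52 attendee comparison |
|---|---|---|
| 0 | slope 1.3, arm A only | biased 0.11 to 0.16 SD in favour of A |
| 0 | half slope, arm A only | biased 0.06 to 0.08 SD in favour of A |
| 0 | slope 1.3, same in the arms compared | bias about 0.00 |
| 0.5 SD worse in A | slope 1.3, same in all arms | estimate 0.43 to 0.44 |
| 0.5 SD worse in A | half slope, same in the arms compared | estimate about 0.48 |
| 0.5 SD worse in A | slope 1.3, arm A only | estimate 0.25 to 0.37 |

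In the first row one-way ANOVA rejected in 7.5% to 12% of runs instead of 5%. In the last row a likelihood-based repeated-measures estimate that included the early termination values returned 0.50; without them it returned 0.44 to 0.47. The 0.50 is partly built in, because leaving was made to depend on exactly the value then supplied. In some runs of the last row, leaving in arm A reached 27% to 29%, well above the planned rate.

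**The case against.** A reader might infer that the plan tests each visit separately on whoever attends, so that leavers vanish. The article does not say this. It names no visit for the continuous comparisons, and a one-way test could be run on a change score, a last available value or the early termination value. This objection stands: the values have no stated place, which is not the same as a stated exclusion. It does not rescue the named tests, because a one-way test on each person's last value would mix week-4 with week-52 scores and still ignore the other visits.

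Analysis sets and missing-data rules commonly sit in an analysis plan or full protocol, so their absence from an article is no fault. That also stands. The choice of test, however, is stated here.

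One-way tests on a single value are valid for randomized arms with complete data, so part of the gain from a repeated-measures model is efficiency. Quality of life, cognition and spirometry are secondary, and PANSS is in neither list of objectives. Adverse events leading to withdrawal are tabulated by arm, so people who leave over tolerability stay visible there. Those counts do not correct a score comparison, but they limit the harm. Leaving for lack of efficacy need not mean a worse PANSS, QLS or BACS.

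Finally, the bias with no true difference and the excess false rejections arise only when the leaving mechanism differs between arms.

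**Conclusion.** The point holds as a poor choice of method for repeatedly measured outcomes, combined with early termination data that are collected but given no stated role. It should be changed, but it does not undermine the smoking outcome, which has its own rule for leavers.

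The size cannot be derived from the article. About 23 of 153 people could be without a week-52 value at the planned drop-out. If leaving follows worsening more in one arm than in the others and there is no true difference, an attendee comparison at week 52 favours that arm by roughly 0.06 to 0.16 SD under the assumed mechanisms. If the mechanism is the same in all arms, the bias with no true difference is about zero, and a true 0.5 SD difference is estimated at about 0.43 to 0.48.

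The stronger conclusion, that the plan will make a product look safer than it is or will inflate false positives, is not supported. It needs both an attendee-only analysis, which the article does not specify, and an arm-specific leaving mechanism, for which it gives no evidence.

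**What to change.** For continuous outcomes with more than one follow-up visit, make the main analysis a mixed model for repeated measures:
- **Terms:** arm, visit, arm-by-visit, the baseline value (the screening value for PANSS) and baseline-by-visit, with unstructured covariance.
- **People:** all randomized participants with any post-baseline value.
- **Early termination values:** assign each to the nearest scheduled visit for that instrument at which the participant has no value. This avoids landing on a visit already attended or one where the instrument is not measured.
- **Contrasts:** weeks 24 and 52 for all four instruments, and week 12 for PANSS. Add week 12 for QLS, BACS and spirometry only once the visit text and Table 1 are reconciled.
- **Sensitivity:** keep Kruskal-Wallis or ANOVA.

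The cost is a change of wording and somewhat more analysis work in the SPSS package already named, with no new data. The model assumes data are missing at random given the observed values, and the plan should say so. The article describes recruitment as still to begin, so the change can be made before any outcome is seen.

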### Study schedule

Participants will attend their study visits at the smoking cessation clinic at approximately the same time of day. With the exception of the BL study day, most visits will take approximately 10 to 15 minutes to complete. The BL visit will be carried out within seven days of the screening visit. At BL (study visit 1), socio-demographic factors, and detailed smoking history will be annotated and individual pack-years (pack/yrs) calculated, together with the ratings of quality of life and neurocognitive functioning assessed by the quality of life scale (QLS) and brief assessment of cognition in schizophrenia (BACS), respectively. Physical cigarette dependence and behavioral dependence will be measured with the Fagerstrom test for cigarette dependence (FTCD) and Glover-Nilsson smoking behavioral questionnaire (GN-SBQ), respectively. Additionally, levels of carbon monoxide in exhaled breath (eCO) will be measured using a portable device (Micro CO, Micro Medical Ltd, Kent, UK). Vital signs (heart rate (HR) and blood pressure (BP)), body weight, spirometry, and AEs will also be recorded at baseline.

Participants will be given a free supply of e-cigarettes or PAIPO inhalators (on average, a 4-week supply of e-cigarettes) and instructed on how to correctly use them. Key trouble-shooting support will be provided and phone numbers will be supplied for medical assistance. A full 4-week supply of nicotine or no-nicotine e-cigarettes, or PAIPO inhalators (depending on the study-arm allocation) will be also provided so that every participant will have enough disposable products for each study period; a study diary recording will be used to check for the most common AEs related to the use of e-cigarettes (for example, dry cough, mouth irritation, throat irritation, headache, shortness of breath, nausea et cetera). No emphasis on encouragement, motivation and reward for the smoking cessation effort will be provided, because this study was intended to monitor schizophrenic smokers who are unwilling to quit. Participants will be instructed to return every four weeks to obtain their 4-weekly supply of e-cigarettes or PAIPO inhalators.

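### Continuous outcomes with a pre-treatment value are compared by covariate-free tests chosen by a normality pre-test, which loses precision and fixes no single estimate per outcome

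*Protocol article*

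**What the plan says.** The Statistical methods section names two routes for continuous data. The general one is: "The differences in continuous variables between the three groups will be evaluated with the Kruskal-Wallis test, followed by the Dunn multiple comparison test". The second, with Newman-Keuls as follow-up, reads: "The differences between the three groups for normally distributed data will be evaluated with one-way analysis of variance (ANOVA". The choice between them rests on one sentence: "The normality of the distribution will be evaluated with the Kolmogorov-Smirnov test". The abstract repeats this scheme. No covariate, baseline adjustment or change-from-baseline analysis is stated for any continuous variable.

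Pre-treatment values are collected for nearly all of these outcomes:

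- Study schedule, baseline visit, quality of life and cognition: "together with the ratings of quality of life and neurocognitive functioning assessed by the quality of life scale (QLS" (the sentence goes on to BACS).
- The same section, exhaled carbon monoxide: "levels of carbon monoxide in exhaled breath (eCO) will be measured using a portable device".
- The same section: "body weight, spirometry, and AEs will also be recorded at baseline".
- The visit summary and Table 1 add cigarettes per day, FTCD, craving and MNWS at baseline.
- Study design places PANSS at screening.

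The same measures return at later visits. Study outcome measures says: "Quality of life, neurocognitive functioning and psychopathological status will be reassessed by QLS, BACS and PANSS, respectively". Baseline enters a stated outcome in one place only, the reducer definition: "A reduction ≥50% in the number of cigarettes/day from BL". That outcome is categorical and goes to a chi-square or Fisher test.

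**The concern.** Two features of the scheme cost something.

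**No baseline term.** Scores such as QLS, BACS or spirometry usually correlate with the same patient's earlier value. A one-way test on follow-up values leaves that predictable between-patient variation in the error term, and chance baseline differences between arms add noise to the estimate. With roughly 44 to 51 patients per arm, the lost precision could decide whether a moderate difference in a secondary outcome is seen.

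**A data-driven choice of test.** ANOVA compares means and Kruskal-Wallis compares ranks. If the trial data decide which is used, the quantity being estimated is not known beforehand. With up to five follow-up visits, one outcome could be compared on means at one visit and on ranks at another. The article does not say whether normality is judged per visit, so this is a possibility rather than a stated rule.

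**Working it through.** **1. The plan's own sample size, to see what it was sized for.** The Sample size section gives effect size 0.30, alpha 0.05, power 0.80, N = 133, and 153 after 15% drop-out. A chi-square test with df = 4 (three arms by reducer, quitter, non responder) needs a noncentrality of 11.935, so N = 11.935 / 0.30² = 132.6, or 133. Then 133 × 1.15 = 152.95, or 153. One-way ANOVA with f = 0.30 and three groups would give 111 instead. The trial therefore appears to have been sized for the categorical outcome, and this point does not alter that number.

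**2. Inputs for the continuous outcomes.**

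- Patients per arm: 133 / 3 ≈ 44 (51 randomized per arm).
- Alpha: 0.05 two-sided (Sample size section).
- Baseline-to-follow-up correlation ρ: not in the document; assumed 0.3, 0.5 and 0.7.
- Pairwise difference: not in the document; assumed 0.5 SD.

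**3. Residual variance after adjustment.** The fraction left is 1 − ρ², which is 0.91, 0.75 and 0.51. The reduction is 9%, 25% and 49%.

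**4. Power, two-sample noncentral t.** Critical value 1.988 with 86 df, and noncentrality = (effect in residual SDs) × √(44/2).

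- Follow-up values only: effect 0.5.
- Adjusted for baseline: effect 0.5 / √(1 − ρ²).
- Change scores: effect 0.5 / √(2(1 − ρ)).

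| ρ | Follow-up only | Change score | Baseline-adjusted |
|---|---|---|---|
| 0.3 | ncp 2.345, 64% | ncp 1.982, 50% | ncp 2.458, 68% |
| 0.5 | ncp 2.345, 64% | ncp 2.345, 64% | ncp 2.708, 76% |
| 0.7 | ncp 2.345, 64% | ncp 3.028, 85% | ncp 3.284, 90% |

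The one error degree of freedom spent on the covariate changes these by about 0.01 percentage point. With 51 per arm, unadjusted power is 71% and adjusted power is 75%, 82% and 94%.

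**5. The same check on a three-arm F test.** Take 130 evaluable patients (153 × 0.85) and an effect that unadjusted ANOVA detects with 80% power (f = 0.275). Adjusted power is 83.8%, 90.4% and 98.0% at ρ = 0.3, 0.5 and 0.7. Change scores give 64.8%, 80.0% and 95.7%. The pattern is the same.

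**6. The pre-test, by simulation.** Skewed data were drawn from a gamma distribution with shape 2, so skewness is 2/√2 = 1.4. At n = 51, plain Kolmogorov-Smirnov with estimated mean and SD rejects normality in about 7-9% of samples across runs. The Lilliefors-corrected version rejects in about 70%. With three arms of 44, all arms are called normal in 84% of simulated trials under the plain version and 5% under Lilliefors. The same data would therefore usually go to ANOVA under one version and to Kruskal-Wallis under the other.

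**7. Type I error of the two-stage procedure.** In 1,500 runs per case, over four distributions and both versions, it lay between 3.8% and 5.7%.

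**The case against.** A reader might infer more than the documents support. Four objections deserve an answer.

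- **The analysis is not invalid.** Randomization keeps the unadjusted tests valid, and the simulated type I error stayed near 5%. Chance baseline imbalance left in the estimate is variance, not bias. This stands, so the point is about efficiency and pre-specification.
- **The trial's main power is not at stake.** Reducers and quitters are categorical, and the reducer definition already uses baseline cigarettes per day. The 133 reproduces as a chi-square. This also stands. The point reaches mainly quality of life, cognition and spirometry, plus supporting continuous measures.
- **Baseline is not necessarily discarded.** The text speaks of differences in continuous variables between groups and does not exclude applying the tests to changes from baseline. This is fair, and at ρ = 0.7 the gain over change scores is only about 5 points (85% to 90%). At ρ = 0.3 and 0.5, however, change scores give 50% and 64% against 68% and 76%, so that reading reduces the loss without removing it.
- **It cannot be said that the pre-test almost never rejects.** That is true of the plain version only, and the article does not name its version. What stands is that the outcome of the gate turns on this unstated detail.

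It is also fair that a linear model need not suit every outcome. Cigarettes per day will contain zeros if patients quit.

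**Conclusion.** The point holds for continuous outcomes with a pre-treatment value: QLS, BACS, spirometry, exhaled carbon monoxide, cigarettes per day, craving, MNWS and FTCD, and PANSS from screening. It does not apply to the satisfaction ratings, which have no baseline.

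Its size depends on ρ, which the documents do not give. At ρ = 0.3 the gain over follow-up-only analysis is modest, about 4 points of power. At 0.5 it is about 12 points and at 0.7 about 26. These figures also assume a 0.5 SD pairwise difference and an unadjusted two-sample test at alpha 0.05, which is not the plan's three-group test with Newman-Keuls or Dunn, so they show scale rather than the trial's actual power. The second half of the point needs none of these assumptions: the stated gate leaves the estimate for each outcome open until the data are seen. This is a worthwhile improvement to a stated choice, not a fatal flaw.

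**What to change.** In the Statistical methods section:

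- Remove the normality gate.
- Name one model in advance for each continuous outcome, with arm and the baseline value (screening value for PANSS) as terms: ANCOVA at a stated visit, or a mixed model across visits. Report adjusted differences with 95% confidence intervals.
- Keep Kruskal-Wallis with Dunn as a pre-stated sensitivity analysis, and as the analysis for the satisfaction ratings.
- For cigarettes per day, pre-state a baseline-adjusted method that copes with zeros, such as a rank-based ANCOVA or a count model.
- Center may be added as a covariate, but the point does not depend on it.

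The cost is analysis wording only, with no new data, visits or patients. The Trial status section says recruitment was still to begin, so the change could be settled before any outcome is seen.
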